Data from 34 innovative projects will be analyzed. Due to the fact that the projects vary in the scope of the intervention they provide, projects are clustered according to the type of their main intervention such as case management, night care, occupational therapy at home and psychological/psychosocial support. These projects might not be considered to be innovative in other countries. The term ‘innovative’ in the context of this research is defined as interventions which are not yet reimbursed by the Belgian NIHDI. These interventions can be seen as alternatives or add-ons to the standard home care services which are already funded (respite care, nursing care at home, physiotherapy, etc.).

The main goal of this study is to identify which types of projects have the most effect in delaying institutionalization of frail older persons.

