### Sample size considerations

Beneficiaries will be grouped by type of projects as shown in Table 1 in order to get a reasonable sample size for each side of the comparison. Using an effect size of 0.50, a two-sided significance level of 0.05 and a power of 85%, 75 participants are needed in each group. We expect each project to include at least 45 participants per year because this is the minimum size of case load projects reported at the beginning of their activities. The clusters of projects will have then a larger sample size than indicated by the sample size calculation.

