### Study population

The study will include older people receiving home care services who are at least 65 years old. Projects are asked to include only clients who are frail and at risk of institutionalization. Due to practical reasons, frailty is measured in the study with two different scales and caregivers are allowed to choose between them. One of these scales is the Edmonton Frail Scale [17,18] with a cutoff point of 6. Another scale is an adapted version of the Katz scale for Belgian home care and residential care [19]. Older people with a Katz score equal to A, B or C will be included [20]. Clients who have been diagnosed with dementia by a geriatrician, neurologist or psychiatrist may also be included in the study.

Each project has to collect data on at least 75% of their total client population in order to ensure representativeness. This means that caregivers have to complete questionnaires for at least 75% of clients benefiting from their projects.

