### Research questions

The aim of the study is to answer the following research questions:

1. Do characteristics of populations differ between projects?

2. Which types of projects are associated with less decrease of the functional and cognitive performance of frail older persons?

3. Which types of projects contribute to a better quality of life of frail older persons?

4. Which types of projects are associated with a decreased risk of institutionalization of frail older persons?

5. Is the interRAI Maple scale a good predictor of institutionalization in our study?

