 The cognitive performance scale (CPS2) is an internationally validated scale that describes a person’s cognitive status. The scores vary from 0 to 6 and the scale consists of 5 items from the interRAI HC instrument: skills for daily decision-making, making oneself understood, short-term memory recall, procedural memory and eating impairment. Higher scores indicate a greater degree of cognitive impairment. Several studies have shown a significant correlation between the CPS scale and the Mini-Mental State Examination (MMSE) [38-41].

 – Research question 4 - Which types of projects are associated with a decreased risk of institutionalization of frail older persons?

In order to answer the fourth research question, the definitive institutionalization (more than 90 consecutive days in residential care) will be used as event. The analysis consists of the calculation of incidence rates, cumulative incidence and hazard rates of definitive institutionalization through survival analyses for each type of project. Survival analysis measures the time to a certain event or change of state, in this case, institutionalization. The multivariate Cox model which will be calculated from this analysis will allow us to isolate the effects of the intervention from the effects of confounding variables. These variables are extraneous variables which correlate (positively or negatively) with both the dependent variable and the independent variable. In this analysis we will use the variables of Table 2 as confounding variables. The use of a Cox model may improve the estimate of the intervention effect by narrowing the confidence interval. Another important advantage of this analysis is that it takes into account the variability of covariates across time which makes it very appropriate for longitudinal studies [42-44].

 – Research question 5 - Is the interRAI Maple scale a good predictor of institutionalization in our study?

The fifth research question will be approached by using a multiple logistic regression model with the Methods for Assigning Priority Levels scale (Maple) as one of the independent variables. This interRAI scale is known to be a predictor for institutionalization and can be used as an indicator for allocation of home care resources and prioritization of clients needing community or residential care. MAPLe is an internationally validated predictor of nursing home placements, caregiver distress and ratings that the client would be better off elsewhere [45].

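### Research question 5 asks how well MAPLe predicts institutionalization, but the only analysis fixed for it gives MAPLe's adjusted association, which does not answer that question

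*Protocol article*

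**What the plan says.** The protocol article lists five research questions. The fifth reads: "Is the interRAI Maple scale a good predictor of institutionalization in our study". Under Analyses, the approach to it is "using a multiple logistic regression model with the Methods for Assigning Priority Levels scale (Maple) as one of the independent variables". The other independent variables are not named for this question. Table 2 is named as the covariate set only for the Cox model of research question 4.

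The rest of the paragraph is background on MAPLe, which it treats as already established: "This interRAI scale is known to be a predictor for institutionalization". It adds that the scale can help to allocate home care resources and to set priorities among clients.

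On who enters the cohort, Study population says: "Projects are asked to include only clients who are frail and at risk of institutionalization". Frailty is judged by the Edmonton Frail Scale or by Katz, at the caregiver's choice. For the Katz route: "Older people with a Katz score equal to A, B or C will be included". MAPLe is not an entry criterion.

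**The concern.** The question is about predictive performance in this cohort. A coefficient in a multiple regression answers a different one: whether MAPLe is still associated with institutionalization once the other variables are held fixed. The two answers can diverge in both directions.

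- With enough events, a weakly discriminating score gets a small p-value.
- If the other variables carry much of the same information, a score that discriminates better on its own can have a modest, non-significant adjusted coefficient.

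The article already treats MAPLe as a known predictor, so another demonstration of association adds little. What is open is how well it works here. The article presents the scale as an aid to prioritization and addresses its findings to care providers and policy makers. A report that MAPLe was, or was not, a significant predictor could be taken as a statement about usefulness that the analysis does not support.

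**Working it through.** **The plan's own figure.** The article has one sample size statement: "Using an effect size of 0.50, a two-sided significance level of 0.05 and a power of 85%, 75 participants are needed in each group". It concerns comparisons between project types, not this question. The normal formula gives 2 × (1.960 + 1.036)² / 0.50² = 71.8, so 72 per group. The exact t-test gives 73, and its power at 75 is 86.0%. The figure is sound but does not bear on question 5.

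**Inputs from the article.** "Data from 34 innovative projects will be analyzed" and "We expect each project to include at least 45 participants per year" give 34 × 45 = 1,530 clients for one year's intake. The 75% data-coverage rule in Study population gives 0.75 × 1,530 = 1,147.

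**Assumed inputs (not in the article).** Institutionalized fraction 5% to 30%; five MAPLe levels; spread 2/5/33/40/20%; odds ratio 1.3 or 1.6 per level.

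**Method.** For a logistic model with MAPLe as a linear score, solve the intercept so that the mean risk equals the event rate. Then z = ln(OR) / SE, with SE from the expected information. The AUC is the sum over levels of (share of events at the level) × (share of non-events below it + half the share of non-events at it).

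**One case in full: OR 1.3, 20% events, N = 1,530.**

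- Risk by level: 10.8, 13.6, 16.9, 21.0, 25.6%.
- Events by level: 1.08, 3.39, 27.96, 41.93, 25.64%.
- Non-events by level: 2.23, 5.40, 34.26, 39.52, 18.59%.
- AUC = 0.0001 + 0.0017 + 0.0692 + 0.2585 + 0.2326 = 0.562.
- z = 0.2624 / 0.0735 = 3.57.

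At OR 1.6 the same steps give z = 0.4700 / 0.0770 = 6.10 and AUC 0.608.

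**Range.**

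| OR per level | Events | z, N = 1,147 | z, N = 1,530 | AUC |
|---|---|---|---|---|
| 1.3 | 5% | 1.67 | 1.93 | 0.56 |
| 1.3 | 10% | 2.31 | 2.66 | 0.56 |
| 1.3 | 20% | 3.09 | 3.57 | 0.56 |
| 1.3 | 30% | 3.56 | 4.12 | 0.56 |
| 1.6 | 5% | 2.86 | 3.31 | 0.61 |
| 1.6 | 10% | 3.95 | 4.56 | 0.61 |
| 1.6 | 20% | 5.29 | 6.10 | 0.61 |
| 1.6 | 30% | 6.09 | 7.04 | 0.61 |

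Within each odds ratio the AUC hardly moves while z more than doubles. A larger intake than one year's would raise z further and leave the AUC where it is.

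**With a second covariate in the model.** The z-values above are for MAPLe alone, so a multiple logistic model was also simulated (N = 1,530, 300 replicates, 10% events, MAPLe spread 3/7/20/45/25%, adjusted OR 1.3 per level, one other covariate).

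| Correlation with MAPLe | MAPLe p < 0.05 | AUC, MAPLe alone | AUC, model without MAPLe | AUC, full model |
|---|---|---|---|---|
| 0 | 81% | 0.564 | 0.636 | 0.654 |
| 0.5 | 65% | 0.616 | 0.661 | 0.671 |

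The adjusted odds ratio is the same in both rows. In the second, MAPLe discriminates better on its own yet reaches significance less often. In both, the full-model AUC exceeds MAPLe's own, because the other covariate supplies much of it.

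**The case against.** The strongest reply is that this is reporting detail. The article says only that the question is approached with a logistic model. It names no odds ratio, test or decision rule, and concordance and risk by level can be obtained from such a model. A condensed article may leave the choice of metric to a fuller document. This stands in part: the absence of an AUC is not itself a finding, and that the coefficient will be the headline is an inference. It does not dispose of the point, because what the article does fix is MAPLe as one variable among several. Even an AUC from that model would credit the other covariates as well as MAPLe.

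Three stronger readings are tempting, and the documents do not support them.

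- *That the cohort is high risk, with a narrow MAPLe spread that by itself lowers discrimination by a known amount.* The article says frail and at risk, gives no MAPLe distribution, and selects on other scales. Any figure depends on the comparator. At 20% events, against an even spread over five levels (AUC 0.603 and 0.675), the loss would be 0.041 and 0.067. Against 10/20/40/20/10% it is 0.016 and 0.027, and against 5/20/50/20/5% about zero. The question is also confined to this study's own clients.
- *That MAPLe is bound to come out significant.* At OR 1.3 and 5% events, z is 1.67 to 1.93, short of 1.96.
- *That overlap with other interRAI scores will mask MAPLe.* Table 2 contains five such scores, but it is assigned to question 4. For question 5 this remains a possibility.

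The passage on resource allocation is background on the scale, not a decision tied to this result.

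**Conclusion.** The point holds as a mismatch between question and method. It rests on the article's wording and needs none of the assumed figures. The numbers show that the gap can matter at the expected caseload: an AUC of about 0.56 is compatible with z from 1.7 to 4.1, and an AUC of about 0.61 with z from 2.9 to 7.0. These ranges depend on the assumed event rate, number of levels, spread and odds ratios. The possible understatement of MAPLe further depends on correlated covariates, which the article does not specify here.

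The weight is moderate. This is the last of five questions and does not touch the main goal of comparing project types. It is still worth changing, because the stated method leaves the stated question unanswered. How unequal follow-up should be handled is a separate matter.

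**What to change.** Reword the analysis for research question 5 as follows.

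1. Main result: the concordance of baseline MAPLe alone with a 95% confidence interval, together with the observed institutionalization risk at each MAPLe level.
2. Next: the gain in concordance when MAPLe is added to the other independent variables, with those variables named.
3. Secondary: the adjusted odds ratio from the multiple logistic model.
4. Show the distribution of MAPLe levels in this frail, at-risk cohort, so that readers can judge the spread instead of assuming it.

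The cost is a few lines of wording and slightly more output from standard software, with no new data. The downside is that reported performance may look less favourable than a significant odds ratio would.

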## Discussion

This paper describes the study protocol of a longitudinal quasi-experimental research to evaluate the effect of innovative projects in delaying institutionalization of frail older persons.

A major strength of the study is the follow up period of 3 years, which allows researchers to obtain a large sample size and several measurement points for a number of clients. Most clients will have at least 3 measurements. Another major strength is the availability of the national database IMA to enable researchers to have a large control group and to have data on health services and medication consumption of the study population. In addition, the use of international validated instruments such as the ZB-12 item, the WHOQOL 8 and the interRAI HC will also make further cross-national comparisons possible.

Some limitations of the study are due to the lack of randomization in the allocation between projects and due to the fact that not all variables collected in the population of the projects will be found in the control group of older persons not benefiting from the projects.

The research will provide knowledge on the functional situation of frail older persons who are still living at home and will allow researchers to make comparisons with older persons who are already institutionalized. This is important information to identify determinants of risk for institutionalization. The identification of effective projects in delaying institutionalization will be useful to inform and empower home care providers, policy and related decision makers to manage and improve home care services.

## Endnote

^a^The NIHDI is a Belgian federal institution which manages and supervises the correct application of the health insurance in Belgium.

## Abbreviations

WHO: World Health Organization; NIHDI: National Institute for Health and Disability Insurance; WHO-QOL-8: World Health Organization Quality of Life instrument 8; ZBI 12: Zarit Burden Interview - 12 items; interRAI HC: interRAI Home Care instrument; IMA: Inter-Mutuality Agency; ADL: Activities of Daily Living; CPS2: InterRAI Cognitive Performance scale 2; IADL: Instrumental Activities of Daily Living; MMSE: Mini-Mental State Examination; sDRS: interRAI Depression Rating Scale.
